### Contamination

Since randomisation takes place at the workers level, the insurance physicians, the labour experts, and the RTW coordinators who are trained in the new RTW program can also be involved in RTW guidance of a sick-listed worker in the usual care group. Therefore, the occupational health care professionals are asked to avoid the use of (components of) the RTW program in the guidance of participants in the usual care group.

### Statistical analyses

All statistical analyses will be performed at worker's level and according to the intention-to-treat principle, i.e. participants will remain in the group (intervention group or control group) to which they were allocated after randomisation at baseline. To check the success of the randomization procedure descriptive statistics will be used, comparing the baseline measurements of both groups. If necessary, analyses will be adjusted for prognostic dissimilarities. To asses the presence of bias due to protocol deviations, the results of the intention-to-treat-analyses will be compared to per-protocol analyses, including only those participants who were treated according to the intervention protocol.

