### The Dutch Social Security System

In the Netherlands the Sickness Benefit Act, carried out by the Social Security Agency (SSA), provides supportive income, i.e. sickness benefit, for workers without an employment contract who become sick-listed. After reporting sick, the worker is entitled to occupational health care by the SSA during his/her sickness benefit period. Vocational rehabilitation is carried out by a team of occupational health care professionals from the SSA, consisting of an insurance physician, a labour expert, and a case-manager. The insurance physician of the SSA guides the worker according to Dutch guidelines for occupational health care. In addition, there are general obligatory occupational health care interventions, as dictated by Dutch legislation, such as inviting to consulting hours, discussing and advising about RTW, and making of a RTW action plan. In principle, when the worker is 6 weeks sick-listed he/she is invited to visit the SSA for a medical assessment by the insurance physician. The aim of this first medical assessment is to certify sickness and thereby approving the sickness benefit claim, and a to make a (medical) problem analysis with advising about recovery, e.g. health promotion, and RTW options. The occupational health care by the SSA ends when the worker is no longer sick-listed and the sickness benefit ends. When the worker is still partially or fully work disabled after two years, he/she can apply for a long-term disability benefit. This is the same as for long-term sick-listed workers with an employment contract.

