### Study population

The population in this study consists of temporary agency workers and unemployed workers, who live in the eastern part of the Netherlands and when sick-listed come under one of the five following front offices of the Social Security Agency: UWV Arnhem, UWV Apeldoorn, UWV Hengelo, UWV Nijmegen, or UWV Zwolle. The main inclusion criteria are: 1. being a temporary agency worker or unemployed worker; 2. being between 18 and 64 years of age; 3. being sick-listed between 2 and 8 weeks; and 4. having MSD as main reason for a sickness benefit claim. The main exclusion criteria are: 1. an accepted sickness benefit claim and being sick-listed for more than 8 weeks; 2. not being able to complete questionnaires written in the Dutch language; 3. having a conflict with the SSA or the Dutch Institute for Benefit Schemes (UWV) regarding a sickness benefit claim or a long-term disability claim, respectively; 4. the presence of a legal conflict, e.g. an ongoing injury compensation claim; and 5. an episode of sickness absence due to MSD within one month before the current sickness benefit claim. After inclusion and randomisation the insurance physician of the SSA is asked to identify workers with severe co-morbidity; i.e. terminal disease, serious psychiatric disorders, or serious cardio-vascular disease, since these are contra-indications for receiving the participatory RTW program. These participants are prevented from starting with the participatory RTW program. However, following the intention-to-treat principle, they remain in the allocated study group (intervention or control). For an overview of all inclusion and exclusion criteria, see table 1.

**Table 1 T1:** Overview of inclusion and exclusion criteria

Inclusion criteria
• temporary agency worker or unemployed worker
• age between 18 and 64 years
• sick-listed between 2 and 8 weeks
• MSD complaints as main reason for reporting sick
• able to complete questionnaires written in Dutch

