### Outcomes

#### Effect evaluation

The primary outcome measure in this study is: duration of the sickness benefit period from the first day of reporting sick until ending of the sickness benefit. Recurrence of sickness absence with an accepted sickness benefit claim within 4 weeks after ending of the previous sickness benefit is considered as belonging to the preceding sickness benefit period, on condition that it is due to the same (or related) MSD. Also, for calculation of the total duration of sickness benefit during the one-year follow-up awarded sickness benefit claims are only included when due to same (or related) MSD.

Secondary outcome measures are:

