#### Effect evaluation

In this study survival analysis will be used to analyse sickness benefit data with regard to the first period of sickness benefit. To describe the duration until ending of sickness benefit in both groups, the Kaplan Meier method will be used. In order to calculate hazard ratios the Cox proportional hazard model will be applied. If necessary, standard errors will be corrected for clustering. Differences in total days of sickness benefit during the one-year follow-up will be analysed with a general linear model. If necessary, the results will be adjusted for dissimilarities at baseline. Longitudinal random coefficient analyses will be used to assess differences in secondary outcome measures. Finally, intraclass correlation coefficients will be calculated at the level of the insurance physician, since the insurance physician plays a key role in acceptance of the sickness benefit claim and the assessment of (sufficient) recovery of functional limitations, i.e work ability, with ending of the sickness benefit.

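### The per-protocol set selects the intervention arm on the primary outcome, so comparing it with intention-to-treat cannot show whether protocol deviations caused bias

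*Protocol article*

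**What the plan says.** Under Statistical analyses, the Protocol article makes intention-to-treat the main approach and adds a second analysis with a stated purpose: "To asses the presence of bias due to protocol deviations, the results of the intention-to-treat-analyses will be compared to per-protocol analyses". The second set is described as "per-protocol analyses, including only those participants who were treated according to the intervention protocol".

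The primary outcome is "duration of the sickness benefit period from the first day of reporting sick until ending of the sickness benefit" (Outcomes, Effect evaluation). For the analysis, "In order to calculate hazard ratios the Cox proportional hazard model will be applied" (Statistical analyses, Effect evaluation).

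Four other places decide who can be treated according to the programme:

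- **Entry.** The worker is included while "being sick-listed between 2 and 8 weeks" (Study population).
- **First consult.** In principle, "when the worker is 6 weeks sick-listed he/she is invited to visit the SSA for a medical assessment" (The Dutch Social Security System). The inventory and brainstorm meetings follow within two weeks (Organisation and preparation), workplace offers within four weeks of contacting the agency (Placement in a matching (therapeutic) workplace), and the coordinator's follow-up call six weeks after the brainstorm (Evaluation).
- **End of care.** "The occupational health care by the SSA ends when the worker is no longer sick-listed and the sickness benefit ends" (The Dutch Social Security System).
- **Contra-indications.** After randomisation the insurance physician identifies workers with severe co-morbidity. "These participants are prevented from starting with the participatory RTW program", although they keep their allocated group for intention-to-treat (Study population).

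**The concern.** Receiving the programme takes weeks, and it can be received only while the outcome event has not yet happened. A worker allocated to it whose benefit ends in week 5 has not deviated from anything; the programme was not yet due. Yet that worker was not treated according to the intervention protocol and falls outside the set as worded. Usual care carries no matching condition. The shortest durations are thus removed from one arm, and membership depends on the quantity being analysed. This is immortal time in the intervention arm.

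At stake is the inference the plan wants to draw. If the per-protocol estimate departs from intention-to-treat when no deviation has biased anything, a gap will be misread as deviation bias. If a second selection happens to cancel the first, agreement will be misread as reassurance.

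**Working it through.** **1. The plan's own figures.** The article gives no number for the per-protocol analysis, but its Sample size section supplies the trial size and event proportion, and these reproduce. For a hazard ratio of 2.0, two-sided 5% and 80% power, the Schoenfeld formula gives 4 × 7.849 / (ln 2)² = 65.3, so 66 events. Then 66 / (2/3) = 99 (stated 100); 100 × 1.10 = 110; and 110 × [1 + (10 − 1) × 0.05] = 110 × 1.45 = 159.5 (stated 160). The check below uses 160 workers, 1:1, with two thirds of benefits ending within a year.

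**2. When the steps fall after reporting sick.** Consult about week 6; brainstorm by about week 6 + 2 = 8 (day 56); workplace offers by about week 8 + 4 = 12; follow-up call at about week 8 + 6 = 14 (day 98).

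**3. How many are removed.** Assume entry at week 4 and a constant hazard ending two thirds of benefits over the next 52 weeks. The share ended by week w is 1 − (1/3)^((w − 4)/52). For weeks 8, 12 and 14 this is 8.1%, 15.6% and 19.0%, or about 6, 12 and 15 of 80 intervention workers.

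**4. Effect on the hazard ratio.** Benefit durations were simulated with no treatment effect. Entry was spread evenly over days 14 to 56, with about two thirds of benefits ending and a constant or falling (Weibull shape 0.7) hazard. The per-protocol set kept all controls and only those intervention workers still on benefit at the threshold. A hazard ratio below 1 means benefit appears to end more slowly with the programme.

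| Must still be on benefit at | Constant hazard | Falling hazard |
|---|---|---|
| day 56 | 0.91 | 0.86 |
| day 70 | 0.86 | 0.79 |
| day 98 | 0.74 | 0.68 |

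Intention-to-treat stayed at about 1.0. A repeat run agreed to within 0.01, and allowing for delayed entry in the Cox model did not remove the bias.

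**5. Error rates and the planned effect.** With entry fixed at week 4 and thresholds at weeks 8, 12 and 14:

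- No true effect: hazard ratio 0.88, 0.78, 0.73 (constant) or 0.82, 0.70, 0.64 (falling). At 160 workers, false significance at the nominal 5% level occurs in 10%, 23%, 32% or 15%, 38%, 52% of trials, almost always against the programme.
- True hazard ratio 2.0: per-protocol 1.76, 1.54, 1.44 or 1.64, 1.39, 1.28, while intention-to-treat stays at about 2.0.

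**6. The opposite selection.** Return to entry over days 14 to 56 with no true effect. Suppose a share of workers has severe co-morbidity, with benefit ending at 0.2 times the hazard of the others, and these too leave the intervention side only. Both the share and the 0.2 are assumptions.

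| Threshold, share removed | Constant hazard | Falling hazard |
|---|---|---|
| day 56, 5% | 0.96 | 0.92 |
| day 56, 10% | 1.03 | 0.98 |
| day 98, 10% | 0.86 | 0.77 |

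**7. The symmetric version.** Restricting both arms to workers still on benefit at the same landmark (week 8, 12 or 14) returns 0.99 to 1.00 when the truth is 1.0, and 1.99 to 2.01 when it is 2.0.

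**The case against.** The strongest reply is that one clause in a journal article does not fix the set. It does not say which steps count as treatment according to the protocol, whether a benefit that ends before the consult counts as a deviation, or how controls qualify. Read literally it could even drop every control. A fuller plan might count early recoverers as compliant. This stands as far as size is concerned, and it is why keeping the controls is stated here as a presumption. It does not rescue the rule: selection is by treatment received, and receipt requires that benefit has not ended.

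Several further objections also stand:

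- The large figures need late thresholds. Placement is described as a possibility, and the article foresees workers still unplaced at the six-week call, so being treated according to the protocol need not mean being on benefit at day 98.
- Week 6 holds only in principle. Workers who enter in weeks 6 to 8 may wait little for the consult.
- A reader might infer that the per-protocol result must be biased against the programme. The documents do not support that. Removing slow recoverers with co-morbidity works the other way and can cancel the effect at day 56. How many such workers remain after randomisation is unknown; Table 1 already lists serious co-morbidity among the exclusions.
- The Study population text refers to either group when it says these workers keep their allocation, so contra-indications may already be identified in both arms.

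**Conclusion.** The concern holds for the supportive analysis and for the inference attached to it. As worded, the per-protocol set selects the intervention arm on benefit duration. That alone moves a true hazard ratio of 1.0 to roughly 0.86–0.91 (day 56) or 0.68–0.74 (day 98). These figures rest on controls being kept, on entry spread over weeks 2 to 8, on the assumed hazard shapes, and on which step is taken as required, which the article does not state. With the co-morbidity exclusion added, the net direction is uncertain if only the early steps count. In the runs here it remained below 1 at day 98.

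A reader might go further and conclude that the trial's main result is compromised. It is not: intention-to-treat is primary, keeps all randomised workers in their groups, and stayed at the true value throughout. Nor does the article tie any decision to the per-protocol result. This should be corrected before analysis, but it is not a threat to the primary conclusion.

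**What to change.** Replace the per-protocol comparison with one that applies the same conditions to both arms:

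- Analyse workers in both arms who are still on benefit at one pre-set landmark day after reporting sick, for example day 56. Inclusion closes at 8 weeks, so every participant has been randomised by then.
- Exclude, in both arms, workers whom the insurance physician identifies as contra-indicated, and confirm that this is recorded for controls too.
- State that benefit ending before a programme step was due is not a protocol deviation.
- Drop the statement that the contrast with intention-to-treat reveals deviation bias.

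If the effect of actually receiving the programme is wanted, add a complier-average estimate with allocation as the instrument. Use a scale that supports it, such as total benefit days or the proportion off benefit at a fixed time, not the Cox hazard ratio. It assumes that allocation acts on the outcome only through receipt of the programme.

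The cost is a change of analysis wording and, at most, one form item completed for controls. The supportive set becomes slightly smaller. The landmark analysis keeps workers who fail to comply later, so on its own it does not measure the effect of adherence. A programme effect already present before the landmark day would also be left out of it.

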#### Effect evaluation

In this study survival analysis will be used to analyse sickness benefit data with regard to the first period of sickness benefit. To describe the duration until ending of sickness benefit in both groups, the Kaplan Meier method will be used. In order to calculate hazard ratios the Cox proportional hazard model will be applied. If necessary, standard errors will be corrected for clustering. Differences in total days of sickness benefit during the one-year follow-up will be analysed with a general linear model. If necessary, the results will be adjusted for dissimilarities at baseline. Longitudinal random coefficient analyses will be used to assess differences in secondary outcome measures. Finally, intraclass correlation coefficients will be calculated at the level of the insurance physician, since the insurance physician plays a key role in acceptance of the sickness benefit claim and the assessment of (sufficient) recovery of functional limitations, i.e work ability, with ending of the sickness benefit.

#### Cost-benefit evaluation

Direct and indirect costs from the insurer's perspective will be calculated for each individual participant. Bootstrapping will be used for pair wise comparing of the group means to calculate mean differences in direct, indirect and total costs between both groups of workers. Confidence intervals (95%) will be computed by bias corrected and accelerated bootstrapping. The mean net monetary benefit (NMB) of the new RTW program compared to usual care will be calculated.

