#### - Direct and indirect costs

Direct costs are paid by the SSA for interventions regarding vocational rehabilitation support, e.g. training/education, for interventions aimed at health promotion, e.g. physical therapy (graded activity) and/or psychological help, or interventions aimed at RTW, e.g. searching for a (temporary) workplace by contracting a vocational rehabilitation agency or temporary placement in work with a willing employer and with an ongoing benefit. Information regarding direct costs is collected from the SSA database and the worker's files after one year of follow-up.

Indirect costs are related to costs due to paid sickness benefit for the sick-listed workers with MSD. When looking at sick-listed temporary agency workers and sick-listed unemployed workers, loss of productivity is not part of the indirect costs. When reporting sick the temporary agency workers immediately falls under the SSA for substituted income, i.e. the sickness benefit. The temporary agency replaces the sick-listed temporary agency worker with a healthy worker at the company/workplace concerned with no productivity loss as a result. Therefore, indirect costs with regard to sick-listed temporary agency workers are the sickness benefit costs paid by the SSA. However, this does not apply to unemployed workers. These workers have no work(place), i.e. there is no productivity. As a consequence, being sick-listed does not result in a productivity loss. Another important fact is that an unemployed worker receives an unemployment benefit. After reporting sick with acceptance of the sickness benefit claim by the SSA, the sick-listed unemployed worker receives a sickness benefit instead of an unemployment benefit. However, the amount of these benefits can differ as this is established using different income conditions. As a result, the sickness benefit can be more than the unemployment benefit. From this perspective, the additional benefit costs are considered indirect costs in this study. Data on paid benefits are collected from the SSA database after the one-year follow-up. Cost-benefit evaluation of the new RTW program is part of this study and will be discussed below.

An overview of the outcome measures and the measurement instruments used, including a time path for all measurements, is presented in table 2.

**Table 2 T2:** Overview of measurements and time path

Measurement	Time path				
	**Baseline**	**3 months**	**6 months**	**9 months**	**12 months**

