### Randomisation procedure

An independent statistician performs the randomisation, using computer-generated randomisation tables. To prevent unequal distribution of relevant prognostic baseline characteristics, before randomisation the sick-listed workers are pre-stratified based on two important prognostic factors, namely type of worker [47-49], i.e. temporary agency worker or unemployed worker, and degree of mental or physical work demands (light or heavy) in last work before current sickness absence[59,60]. Next, block randomisation (using blocks of four allocations) is applied to ensure equal group sizes within each stratum. A separate block randomisation table is generated for each of the five participating front offices of the SSA. Next, the researcher prepares for each stratum opaque sealed envelopes, containing either a referral to the new RTW program group or to the usual care group. After informed consent and completing the baseline questionnaire, the temporary agency worker or unemployed worker is asked to choose one of the two succeeding envelopes of the correct stratum. Then, the worker is asked to open the envelope and write down his/her name and date on the note with the randomisation result.

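### The cost comparison leaves worker type and daily benefit cost unadjusted, so its intervals are wider than the data require; the estimate itself is unbiased.

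*Protocol article*

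**What the plan says.** Under Statistical analyses, Cost-benefit evaluation, the protocol article plans: "Bootstrapping will be used for pair wise comparing of the group means to calculate mean differences in direct, indirect and total costs". It adds that "Confidence intervals (95%) will be computed by bias corrected and accelerated bootstrapping". Neither sentence names a covariate or a stratum.

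The outcome section on direct and indirect costs defines indirect cost differently for the two kinds of worker:

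- Agency workers: "indirect costs with regard to sick-listed temporary agency workers are the sickness benefit costs paid by the SSA".
- Unemployed workers, who move from unemployment benefit to sickness benefit: "the amount of these benefits can differ as this is established using different income conditions", and only "the additional benefit costs are considered indirect costs in this study".

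On the source, it says: "Data on paid benefits are collected from the SSA database after the one-year follow-up".

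The Randomisation procedure pre-stratifies on "type of worker [47-49], i.e. temporary agency worker or unemployed worker, and degree of mental or physical work demands (light or heavy"), with a separate block table for each of the five front offices.

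One clause at the head of the Statistical analyses section covers all analyses: "If necessary, analyses will be adjusted for prognostic dissimilarities".

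**The concern.** A worker's indirect cost is the number of benefit days times an effective daily cost: the sickness benefit for an agency worker, or its excess over unemployment benefit for an unemployed worker. The program aims to shorten the days. The worker's type is known before allocation. The daily cost can reasonably be taken as settled by then too, although the documents do not say so.

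A bootstrap of raw means treats all of this variation as noise. For worker type there is a further mismatch. Allocation in blocks of four within strata keeps the type mix close to equal between arms, but an unstratified bootstrap lets it vary freely. The interval then reflects a source of imbalance that the design largely removes.

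At stake is the width of the intervals for indirect cost, total cost and net monetary benefit. The sample size was set for the hazard ratio and not for costs, so there is no planned reserve of precision here. The general adjustment clause does not fill the gap, because it responds to imbalance seen at baseline and does not plan adjustment for precision.

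**Working it through.** **The plan's own figure.** The plan states no standard deviation, precision or power for costs. Its sample size concerns the primary outcome: 4 × (1.96 + 0.84)² / (ln 2)² gives 66 events, and 66 / (2/3) = 99, against a stated 100. Only the two-thirds premise is carried forward.

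**Inputs**

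- From the plan: two thirds end benefit within 365 days; two groups of 80.
- Assumed: exponential time to end of benefit; days independent of the daily amount; daily amount set before randomisation; coefficient of variation k of the daily amount 0.2 to 0.5.
- Assumed for the mix: half the workers unemployed; agency mean daily amount 50 (arbitrary units); unemployed excess drawn as the absolute value of a normal variable with mean 8 and SD 8, so that it cannot be negative (mean 9.33, mean square 64 + 64 = 128).

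**Step 1: benefit days.** Rate = ln 3 / 365. Days capped at 365 have mean about 221 and SD about 131, so CV = 0.593 and CV² = 0.352.

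**Step 2: agency workers only.** The share of cost variance explained by the daily amount is R² = k² / (k² + 0.352 + 0.352k²). The ratio of adjusted to raw interval width is √(1 − R²).

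| k | R² | Width ratio |
|---|---|---|
| 0.2 | 0.040/0.406 = 0.10 | 0.95 |
| 0.3 | 0.090/0.474 = 0.19 | 0.90 |
| 0.4 | 0.160/0.568 = 0.28 | 0.85 |
| 0.5 | 0.250/0.690 = 0.36 | 0.80 |

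The interval is 5% to 20% narrower. R² reaches one half only at k of about 0.74. A bootstrap simulation with 80 per arm, and benefit ending 1.5 times as fast in the intervention arm, gave ratios of 0.96, 0.91 and 0.86 for k = 0.2, 0.3 and 0.4.

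**Step 3: 50/50 mix.** Let e be the effective daily cost. In units of squared mean days:

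- cost variance = 1.352 E[e²] − E[e]²
- part explained by e = E[e²] − E[e]²
- part explained by type = ((50 − 9.33)/2)² = 413.4
- E[e] = (50 + 9.33)/2 = 29.67, squared 880.1
- E[e²] = 1250(1 + k²) + 64

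| k | E[e²] | Cost variance | R², type | Width ratio, type | R², effective cost | Width ratio, effective cost |
|---|---|---|---|---|---|---|
| 0.2 | 1364 | 964 | 413/964 = 0.43 | 0.76 | 484/964 = 0.50 | 0.71 |
| 0.5 | 1626.5 | 1319 | 413/1319 = 0.31 | 0.83 | 746/1319 = 0.57 | 0.66 |

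Type alone narrows the interval by 17% to 24%, and effective daily cost by 29% to 34%. Under the independence assumption type adds nothing once effective cost is in. It belongs in the model because durations may differ by type.

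**Step 4: sensitivity.** With 30% to 70% unemployed, an excess of 0% to 30% of the benefit, k of 0.2 or 0.4 and the same 1.5-fold program effect, the width ratio was 0.64 to 0.91 for type alone and 0.61 to 0.84 for effective daily cost. For the raw sickness benefit rate alone it was only 0.91 to 0.995. The direction never changed.

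**The case against.** The strongest reply is that nothing here is wrong. Under randomisation the raw difference in mean cost is unbiased for the insurer's cost, and the bootstrap interval already allows for chance differences in benefit amount. The general clause permits adjustment in any analysis. The baseline list is open-ended and already includes education, previous work and working hours, which may track income. All of this stands, and it limits the point to efficiency. It does not remove the point: the article specifies raw means for costs, and the clause is conditional on observed dissimilarity.

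A reader might infer that each worker's cost is largely set by a daily amount fixed by past income. The documents do not support that. They give no amounts or spread and say only that the two benefits rest on different income conditions. Within agency workers, days carry most of the variance at every k tried. The better-documented source of predictable variance is worker type.

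A reader might also infer that a chance income difference between arms would distort the result. With k = 0.3, the standard error of that difference is 0.3 × √(2/80) = 4.7%, or about 10 benefit days when days are costed in full. That is ordinary sampling error, which the interval already covers.

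The calculations cover indirect cost only. Direct costs have no evident link to the daily amount, so the gain for total cost and net monetary benefit will be smaller by an amount the documents do not allow one to compute.

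**Conclusion.** The point holds as one of precision. The planned cost comparison ignores a stratification factor that determines how indirect cost is defined, and a daily cost that can be known at randomisation, so its interval is wider than necessary. For indirect cost the adjusted interval would be about 5% to 20% narrower among agency workers. In an even mix it would be about 17% to 24% narrower with type alone and 29% to 34% narrower with effective daily cost added. These figures rest on the plan's two-thirds premise and on assumed benefit amounts, spreads, worker mix and independence; the direction is secure and the size is not. The point estimate is not biased, and no conclusion drawn from the unadjusted analysis would be invalid.

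**What to change.** In the statistical section on cost-benefit evaluation:

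- Resample within arm and worker type.
- In each bootstrap sample, regress cost on arm, worker type and the effective daily benefit cost in force at randomisation. This is the sickness benefit for agency workers and its excess over unemployment benefit for unemployed workers. The raw sickness benefit rate alone is not a substitute.
- Take the bias-corrected and accelerated interval of the arm coefficient for indirect cost, total cost and net monetary benefit.
- Report the unadjusted mean differences alongside.

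The cost is the extraction of benefit rates at randomisation from the agency data already used for costing, including the unemployment benefit that the excess requires, and a slightly more complex bootstrap.
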